## Methods

### Study Design and Setting

The SmaVTE study is a 2-armed, single-center, parallel-group, randomized controlled trial designed to evaluate the impact of the mVTEA app on the KAP of patients with or at high risk of VTE. The trial will be conducted at the Sixth Medical Center of the Chinese People’s Liberation Army General Hospital, which is a tertiary hospital that integrates medical care, teaching, and research. A total of 256 hospitalized patients with or at high risk of VTE will be recruited on the day of their discharge. Participants will be randomly allocated in a 1:1 ratio to either the mVTEA management group or the routine management group. The mVTEA management group (n=128), also referred to as the experimental group, will receive patient-centered VTE management facilitated by the mVTEA app after discharge. In contrast, the routine management group (n=128), also known as the control group, will be administered with conventional postdischarge management according to local clinical practice. All of the above management will be performed for 3 months following discharge. Our study is scheduled to commence in August 2024 and conclude in November 2025. Recruitment began in August 2024 and is anticipated to conclude by June 2025. Data analysis is planned to commence in October 2025 after the follow-up data collection. The analysis is expected to be completed by November 2025. The protocol conforms to the SPIRIT (Standard Protocol Items: Recommendations for Interventional Trials) 2013 statement [37]. The latest protocol (version 1.0) was dated March 1, 2024. The trial was registered on Clinicaltrials.gov (NCT06350331).

### Participants and Recruitment

Potentially suitable candidates for the study will initially be screened from the inpatients in departments at high risk of VTE through the clinical decision support system for VTE risk assessment and integrated care in our hospital [38]. Based on the initial screening list, a final identification of whether the patient meets the study recruitment needs will be made on the day the patient is discharged from the hospital. Patients who fulfill the recruitment criteria and are willing to participate will receive comprehensive information about the entire study protocol, including its benefits and potential risks. Once patients agree to participate, they will be directed to a web-based informed consent document or, depending on the subject’s wishes, a paper version of the informed consent document will be given at the same time. This recruitment process will be carried out with the utmost respect for the individual preferences of each participant. In addition, we assure that the rights of participants to withdraw from the study will be upheld throughout all phases of the clinical trial. The inclusion and exclusion criteria of the study are shown in Textbox 1.

Inclusion and exclusion criteria.
**Inclusion criteria**
Inpatients ≥18 years of age at admission.Previous or current definitive diagnosis of deep vein thrombosis (DVT), pulmonary embolism (PE), both by imaging, or high risk of venous thromboembolism (VTE) at discharge: Padua score ≥4 for medical patients and Caprini score ≥5 for surgical patients.Signed informed consent.
**Exclusion criteria**
Mental disorder or a combination of other serious diseases leading to incapacity for independent living.Inability to use smartphones, computer tablets, and other smart devices.Being pregnant or breastfeeding.Have participated in similar trials or are undergoing other clinical trials.

### Randomization

Stratified block randomization was used to allocate participants. Participants were divided into 4 strata based on 2 factors: age (≥60 years and <60 years) and their VTE diagnostic status at the time of recruitment. The strata consist of (1) patients aged ≥60 years diagnosed with VTE, (2) patients aged ≥60 years at high risk for VTE but not diagnosed, (3) patients aged <60 years diagnosed with VTE, and (4) patients aged <60 years at high risk for VTE but not diagnosed. Within each stratum, participants were assigned in a 1:1 ratio to either the mVTEA management group or the routine management group. This allocation was performed using a fixed block randomization method with a block size of 4. The random sequence was generated by a free, robust randomization app with a random seed number of 20240215 [39]. A web-based random allocation system was used to assign random numbers to each participant.

### Blinding

Due to the limitations of the protocol and the specific nature of mHealth management, it is not feasible to blind participants, their primary care physicians, and clinic physicians. However, to enhance the quality and reliability of this study, the researchers will be blinded during the efficacy assessment, data collection, data management, and statistical analysis of the results. Therefore, those responsible for efficacy assessment, data collection and management, and analysis of results will not be informed of trial group assignments and will not be permitted to communicate with each other or with participants about the treatment. Furthermore, to minimize potential bias introduced by unblinded participants or researchers, the study will include only individuals who have no conflict of interest.

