#### Routine VTE Management

The routine VTE management group will receive only conventional postdischarge management according to local clinical practice, including basic health advice appropriate for the prevention and treatment of VTE. The textual and graphical materials comprising the aforementioned basic package for VTE-related health education in the mVTEA app will be printed and distributed to patients within the routine management group on the day of discharge for home-based study. The video courses in the health education basic package can be accessed by scanning the QR code.

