#### Secondary Outcomes

Secondary outcomes include scores on each domain of the VTE-KAP questionnaire (knowledge domain, attitude domain, practice domain), QoL, VTE events, chronic thromboembolic pulmonary hypertension, chronic thromboembolic pulmonary disease, post-PE syndrome [13,48], International Society on Thrombosis and Hemostasis (ISTH) defined major bleeding events [59], VTE-related hospitalizations, VTE-related rehospitalizations, all-cause deaths, PE-related deaths, and new-onset of atrial fibrillation (AFI) or atrial flutter (AFL) at 3-month follow-up. For patients with more than 1 event, only the first event will be counted. A total of 3 investigators who are unaware of patients’ group assignments will adjudicate all endpoints.

Generic, nondisease-speciﬁc health-related QoL is assessed using the EQ-5D-5L questionnaire and its corresponding visual analog scale [60]. Brieﬂy, the EQ-5D-5L generates an overall index that ranges from 0 (lowest generic QoL) to 1 (highest generic QoL) and is calculated based on country-speciﬁc reference value sets. The EQ-5D-5L health index was calculated with the value set for China. The EuroQol visual analog scale ranges from 0 to 100, with higher scores indicating better health.

VTE events are categorized into 3 groups: new-onset VTE, hospital-acquired VTE (HA-VTE), and recurrent VTE. VTE that occurred for the first time during the study period is classified as new-onset VTE. HA-VTE is defined as any new-onset VTE that has occurred within 90 days of hospital discharge [4]. Recurrent VTE is defined as the appearance of new evidence of VTE after acute VTE has been treated in the acute phase (2 weeks) with significant clinical improvement in signs and symptoms. According to the time of VTE recurrence, it is further categorized into early VTE recurrence (within 3 months after the last VTE occurrence) and late VTE recurrence (more than 3 months after the last VTE occurrence) [61]. Hospitalization due to the new-onset VTE will be documented as VTE-related hospitalizations, while rehospitalization due to VTE recurrence, progression, or complications arising from VTE treatment will be classified as VTE-related rehospitalizations. All-cause death refers to any death occurring during the study period, regardless of the cause. PE-related death is defined as death explicitly caused by PE.

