New-onset AFI or AFL is defined as an episode of AFI or AFL lasting at least 30 seconds, first detected by devices such as smart wearable devices or ambulatory electrocardiograms, or initially diagnosed during a medical visit and documented in outpatient charts or inpatient hospital records.

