### Data Collection and Management

Table 3 presents the detailed schedule for data collection and assessments. Baseline demographic and clinical data will be extracted from the hospital information system. Additional data—including mHealth use, electronic health literacy, EQ-5D-5L, and VTE-KAP—will be collected at discharge and follow-up via web-based questionnaires for the routine group and through the mVTEA platform for the intervention group. The Chinese version of the electronic health literacy scale (C-eHEALS) will be used to evaluate participants’ eHealth literacy [62]. Follow-up at 3 months postdischarge will be conducted through outpatient visits, telephone interviews, or web-based interviews via the mVTEA platform (for the intervention group). All collected data will be deidentified and recorded in electronic case report forms. Data will be securely stored on password-protected servers with restricted access, and sharing with third parties will require authorization from the corresponding author. The quality control team will routinely verify data accuracy and reliability; upon confirmation, the data will be locked to prevent further modifications. The finalized database will be provided to statistical analysts as specified in the statistical analysis plan. All data collectors and managers will undergo standardized training and assessment before participating in the study.

**Table 3 table3:** Study protocol, schedule, and timing of data collection.

Activity or assessment	Screening (during hospitalization, t_1_)	Enrollment (at discharge, 0)	Study visit (at discharge [intervention], t_1_)	Follow-up (3rd month, t_2_)
Prescreening consent	✓			
Eligibility screen	✓			
Informed consent		✓		
Randomization		✓		
Demographic information		✓		
Medical history		✓		
mHealth use		✓		
C-eHEALS^a^		✓		
VTE^b^-KAP^c^ questionnaire		✓		✓
EQ-5D-5L		✓		✓
Interventions				
Basic health education			✓	
mVTEA^d^-assisted management			✓	✓
Routine management			✓	✓
VTE event				✓
CTEPH^e^				✓
CTEPD^f^				✓
PPES^g^				✓
Bleeding event				✓
VTE-related hospitalization				✓
VTE-related rehospitalization				✓
Death				✓
New-onset of AFI^h^ or AFL^i^				✓
Adverse event				✓

^a^C-eHEALS: Chinese version of the electronic health literacy scale.

^b^VTE: venous thromboembolism.

^c^KAP: knowledge, attitude, and practice.

^d^mVTEA: smart technique-assisted patient-centered care mHealth app for managing venous thromboembolism.

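### Data collectors and data managers are said to be blinded, but the month-3 interview platform and the questionnaire routes differ by arm and reveal the allocation

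*Protocol article*

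**What the plan says.** The Blinding section accepts that "it is not feasible to blind participants, their primary care physicians, and clinic physicians". As compensation it promises that "the researchers will be blinded during the efficacy assessment, data collection, data management, and statistical analysis of the results", and adds that "those responsible for efficacy assessment, data collection and management, and analysis of results will not be informed of trial group assignments". It also bars these staff from discussing treatment with one another or with participants.

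The Data Collection and Management section gives three routes for the month-3 follow-up: outpatient visit, telephone, or "web-based interviews via the mVTEA platform (for the intervention group". It collects the survey data, including VTE-KAP and EQ-5D-5L, at discharge and at follow-up "via web-based questionnaires for the routine group and through the mVTEA platform for the intervention group". It says that collected data will be deidentified and entered in electronic case report forms.

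The Routine VTE Management section says that "The routine VTE management group will receive only conventional postdischarge management according to local clinical practice". Under Quality Control, a dedicated follow-up office carries out the follow-ups. Under Secondary Outcomes, "A total of 3 investigators who are unaware of patients’ group assignments will adjudicate all endpoints". The Limitations section concedes that double blinding was not possible and relies on blind statistical analysis and separation of roles.

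**The concern.** Two statements about the same staff do not fit together. One says that data collectors and managers do not know the arm. The other has them work through channels that differ by arm, one of which is reserved for the intervention group. Not telling someone the allocation does not blind them if the tool they work with discloses it.

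Table 3 schedules VTE events, bleeding, VTE-related admissions, death and new-onset atrial fibrillation or flutter for ascertainment at month 3. Some of these begin with what the patient is asked and what the interviewer writes down. An interviewer who knows the arm may probe more or less for leg symptoms or minor signs of bleeding. Masked adjudication cannot repair this, because adjudicators see only what was elicited and recorded. The study hypothesis includes patient safety, so uneven ascertainment of these events bears on a stated claim. Readers would also credit the trial with a safeguard that some of its staff do not have.

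**Working it through.** No figure in the plan depends on this point, so the check compares the sections role by role.

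1. **Platform interviewer at month 3.** The Blinding section counts data collectors as blinded. The Data Collection and Management section offers the platform interview to the intervention group only, and the routine arm has no app-based management. Platform interview therefore implies intervention arm, with certainty. The blinding statement fails for this role.

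2. **Outpatient or telephone contact.** Both routes are open to both arms, so the route itself reveals nothing. However, the Blinding section names clinic physicians as unblinded, so an outpatient contact is arm-neutral only if someone else ascertains the events.

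3. **Collector or manager handling questionnaire source records.** VTE-KAP and EQ-5D-5L arrive by one channel in one arm and by another in the other arm, at both time points. Anyone who sees the channel can infer the arm. The statement fails for those who see source records. It can hold for those who see only records from which the channel has been removed.

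4. **The three adjudicators and the statisticians.** The article does not describe the adjudication file or say whether the analysis file carries the collection route. Deidentified electronic case report forms make masking feasible. Their blinding is conditional on the files carrying neither route nor arm.

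5. **Primary outcome.** VTE-KAP is self-administered by patients who know their arm. No interviewer scores it, so the interview route neither creates nor removes its reporting bias.

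**Exposure.** With 128 patients per arm, between 0 and 128 intervention patients can be followed by the revealing route, against 0 of 128 in the routine arm. The plan does not say how many will use it.

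**Outcomes affected.** Outcomes that depend on questioning (VTE symptoms, bleeding) are most exposed. Deaths and admissions are less so, since they depend less on how a patient is probed.

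**Room to change.** At submission 185 of 256 patients were enrolled, so at least 256 − 185 = 71 month-3 contacts were still to come at that point.

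**The case against.** The strongest reply is that the conflict is narrow. The Limitations section admits that double blinding was impossible and claims only blind analysis and segregated roles. Data are deidentified before they reach analysts, and adjudicators are separately stated to be unaware of the arm. The affected outcomes are secondary, and the article itself says that they need confirmation in later research. Staff are also forbidden to discuss treatment with participants. Changing the route during the trial would mix follow-up methods within the app arm, whereas correcting the text would need no change in conduct.

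Most of this stands as a limit on scope. None of it removes the conflict for platform interviewers or for those who see source records. The ban on discussing treatment helps on the telephone, but it does nothing where the platform itself discloses the arm.

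A reader might infer three stronger things that the documents do not support:

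- That adjudication and analysis are unblinded too. Nothing describes the material given to these people, and masked files are feasible.
- That the atrial fibrillation definition ("first detected by devices such as smart wearable devices or ambulatory electrocardiograms") adds evidence. It says nothing about blinding or follow-up route, and it also accepts diagnoses documented in outpatient or inpatient records.
- That a small-count example gives the size of the bias. Suppose 3 against 3 events become 4 against 2: the risk ratio moves from 1.0 to (4/128)/(2/128) = 2.0. Those counts are invented and need errors in opposite directions in the two arms. The log-scale standard error is √(1/4 − 1/128 + 1/2 − 1/128) = 0.857, so the 95% CI runs from about 0.37 to 10.7. It does not measure this trial's bias.

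**Conclusion.** The point holds for two groups: with certainty for anyone who conducts a month-3 interview on the mVTEA platform, and by inference for data collectors or managers who see the source of the records. For these roles the Blinding section and the Data Collection and Management section cannot both be right. Adjudicators and statisticians can remain blinded if their files carry no route or arm.

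The consequence is possible differential elicitation of interview-dependent secondary events. Its size and direction cannot be computed, because the documents give neither platform uptake nor event rates; 128 app-arm patients is a ceiling and not an estimate. The primary comparison does not turn on this point, since VTE-KAP is self-reported by unblinded patients whatever the follow-up route. The conclusion assumes that the platform restriction means what it says and that the follow-up staff count as data collectors. The point should be corrected because the plan offers staff blinding as its compensation for unblinded participants.

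**What to change.** **Conduct.** For the remaining month-3 contacts, have the existing follow-up office ascertain events in both arms by the same arm-neutral route already allowed. Scripted telephone contact by staff not told the arm would serve. Ascertainment should not fall to the unblinded clinic physicians. For patients already followed, record the route used and report it by arm.

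**Files.** Remove collection route and platform name from what data managers, adjudicators and analysts receive. This also deals with the arm-specific questionnaire channels, which need not change.

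**Text.** Restate the Blinding section so that blinding is claimed only for the roles that have it, and say how route and arm are masked for them. State that VTE-KAP and EQ-5D-5L are self-reported by unblinded patients through arm-specific routes.

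**Cost.** App-arm patients lose some convenience, and follow-up routes will be mixed within that arm because some patients may already have been interviewed on the platform. The office and the neutral route already exist, so the added work is a script, a route field and redaction. Rewording alone would make the statement accurate at almost no cost, but it would leave the uneven ascertainment in place.

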### Intervention

#### Overview

The mVTEA management group will receive patient-centered VTE management facilitated by the mVTEA app based on the combination of HBM and KAP frameworks after discharge, while the routine management group will undergo conventional postdischarge management according to local clinical practice. In addition, VTE management using the mVTEA app is administered by certified thrombosis specialists and nurses with over 5 years of clinical experience and proficiency in operating the mVTEA app. Furthermore, regular training sessions and assessments on VTE prevention and treatment for health care professionals are conducted in our hospital, along with routine quality control meetings focused on VTE prevention and treatment. These measures ensure that all health care professionals in our hospital possess the necessary competencies to effectively implement VTE prevention and treatment.

#### Integrated VTE Management Pathway Within mVTEA

The long-term management of VTE is multifaceted, requiring individualized patient assessment and a nuanced approach to therapy. In this study, we have proposed the ABCDEF pathway for integrated management of VTE to complement mVTEA-assisted patient-centered management, thus minimizing the risk of VTE and its complications and ensuring patient safety and quality of life (QoL): (1) appropriate antithrombotic management; (2) bleeding risk management; (3) complication monitoring; (4) digital health management; (5) exercise and rehabilitation; and (6) facilitate the management of risk factors and comorbidities. Details of the integrated VTE management pathway are presented in Table 1.

**Table 1 table1:** The ABCDEF pathway for integrated management of venous thromboembolism.

Pathway and key point			Process
**Appropriate antithrombotic management [13,40-46]**			
	Thrombosis risk management	Monitor patients’ thrombotic risk after discharge to facilitate thrombosis prevention, improve treatment decisions, and enhance patient self-management.	
	Anticoagulant therapy selection	Choose the appropriate anticoagulant (eg, warfarin or DOACs^a^) based on individual patient risk factors, renal function, and potential drug interactions.	
	Dose adjustment and monitoring	Conduct regular blood tests (eg, INR^b^ for warfarin and renal function tests for DOACs) and patient consultations to monitor therapeutic effects. Schedule follow-ups to reassess and adjust dosages based on test results and patient feedback.	
	Thromboprophylaxis	Assess patient risk factors to determine the need for prophylaxis, administer appropriate prophylactic measures, and monitor their effectiveness.	
**Bleeding risk management [13,14,40-47]**			
	Bleeding risk assessment	Conduct a thorough bleeding risk assessment using validated tools (eg, HAS-BLED^c^ score) before initiating anticoagulant therapy and reassess periodically.	
	Personalized anticoagulant therapy	Tailor anticoagulant therapy to the individual’s bleeding risk, opting for agents with lower bleeding risk profiles if necessary.	
	Bleeding precautions	Implement preventive measures such as avoiding unnecessary invasive procedures and managing concurrent medications that may increase bleeding risk.	
**Complication monitoring [13,44,48,49]**			
	Regular complication surveillance	Schedule regular check-ups and use diagnostic imaging (eg, Doppler ultrasound, CTPA^d^) to monitor for complications such as recurrent VTE^e^, PTS^f^, PPES^g^, or CTEPH^h^.	
	Patient self-monitoring	Encourage patients to report new or worsening symptoms promptly, and provide them with clear instructions on what to look out for.	
**Digital health management [22-24,50]**			
	Telemedicine	Implement telemedicine platforms for regular follow-ups, reducing the need for in-person visits and enabling remote monitoring of anticoagulation therapy.	
	mHealth^i^ apps	Use mHealth apps that allow patients to track their medication adherence, report symptoms, and receive reminders for follow-up appointments.	
	Wearable devices	Encourage the use of wearable devices that monitor vital signs (eg, heart rate and oxygen saturation) to detect early signs of complications.	
